#### Primary endpoint

The primary outcome will be a composite clinical efficacy end-point related to implantation success at hospital discharge, based on the VARC-2 criteria [37]Absence of procedural mortalityCorrect positioning of the prosthetic valveIntended performance of the prosthetic valve (mean aortic valve gradient < 20 mmHg and no valve regurgitation > mild)

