## Statistical methods {20a}

Statistical analysis will be performed with SPSS 26.0. (IBM, Armonk, NY, USA) for Windows.

Statistical analysis will be supervised by an independent statistician from the Department of Medical Statistics, Informatics and Health Economics (Innsbruck Medical University). Normally distributed continuous variables will be presented as mean ± standard deviation, not normally distributed continuous variables as median with corresponding interquartile range (IQR). Categorical variables will be displayed as the number and percentage of patients. Pearson or Spearman correlations will be calculated as appropriate. *χ*^2^-test will be used to compare categorical variables between groups. ANOVA with Bonferroni post hoc testing (if ND) and Mann–Whitney-*U* (if not ND) will be used to determine differences in continuous variables between groups. Time-to-event is defined as time from the TAVR procedure to the date of the first end-point. Kaplan–Meier survival curves will be determined and log-rank comparison will be used between groups. Uni- and multivariate Cox-regression analysis will be used to estimate hazard ratios for all left ventricular variables. Factors with univariate association with the primary end-points with significance < 0.1 will be entered in multivariate analysis. For all data a 2-tailed *p*-value of *p* < 0.05 will be considered to indicate statistical significance. No interim analysis is planned.

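### The stated Cox analysis does not fit the trial: it targets left ventricular variables, screens covariates at p < 0.1 against a yes/no discharge endpoint, and is not directed at CMR versus CT

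*Protocol article*

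**What the plan says.** All the regression text is in the protocol article, Statistical methods {20a}. It first defines the time axis: "Time-to-event is defined as time from the TAVR procedure to the date of the first end-point". It then compares the arms: "Kaplan–Meier survival curves will be determined and log-rank comparison will be used between groups". The regression follows: "Uni- and multivariate Cox-regression analysis will be used to estimate hazard ratios for all left ventricular variables". The entry rule comes next: "Factors with univariate association with the primary end-points with significance < 0.1 will be entered in multivariate analysis". For categorical data, the same section says that a chi-square "test will be used to compare categorical variables between groups".

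Under Primary endpoint there is one endpoint, a composite "related to implantation success at hospital discharge, based on the VARC-2 criteria". Its components are no procedural death, correct valve position, and valve performance within gradient and regurgitation limits.

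Under Objectives {7}, item (c) extends the non-inferiority question on efficacy and safety to 2 years. Under Secondary endpoints, the combined safety and clinical efficacy composites are read at discharge and at 2 years.

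**The concern.** Three things in the Cox text do not match the rest of the article.

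- **Endpoint.** The entry rule refers to primary endpoints in the plural. The article has one, and it is a success/failure status at discharge. Cox regression needs an event time.
- **Covariates.** The hazard ratios are for left ventricular variables, which appear in no objective and no endpoint. The word used is all, so the candidate list is open.
- **Target.** The trial asks about CMR versus CT. The only regression stated does not name imaging strategy as a term.

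Two things are at stake. The 2-year non-inferiority objective needs an effect estimate with an interval, and the natural source of one is pointed elsewhere. Selecting covariates by p-value on the trial's own outcome, with few events, can also admit noise and produce intervals that ignore the selection step.

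**Working it through.** **1. The plan's own figure.** Sample size {14} gives 92% success in both arms, a 9-point margin, 80% power and 113 per group. The formula is n = (z₁₋α + z₀.₈₀)² × 2 × 0.92 × 0.08 / 0.09². At one-sided α = 0.05 this is (1.645 + 0.842)² × 0.1472 / 0.0081 = 112.4, which rounds up to 113. The figure is reproduced and uses no Cox model, so this point does not touch the sample size.

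**2. Does the primary endpoint have an event time?** Time zero is the TAVR procedure. Correct positioning is decided at the procedure, that is, at time zero. Gradient and regurgitation are a status read by discharge. Only procedural death has a natural date. An event time for the composite would therefore mostly reflect when the assessment was made or how long the patient stayed. The 2-year composites include death, stroke and hospitalisation, where time-to-event methods can apply. If Cox regression is meant for those, the entry rule names the wrong endpoint. The text needs correcting on either reading.

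**3. Do left ventricular variables serve a stated question?** Objectives (a) to (e) cover implantation success, safety, 2-year follow-up, imaging procedure variables and measurement accuracy. The endpoint lists contain no left ventricular variable. The CMR and CT data analysis section lists valve morphology, annulus, coronary heights and aortic and iliac sizing. It mentions the left ventricular chamber only as part of the volume rotated to take those measurements.

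**4. Which arm comparisons are stated?** They are chi-square, and Kaplan–Meier with log-rank. The section applies a two-sided 5% significance level throughout ("For all data a 2-tailed" p-value). The two tests ask whether the arms differ. No between-arm effect size with a confidence interval is stated for the 2-year composites.

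**5. Events available if the rule is applied to the discharge endpoint.** Inputs are 226 analysed (Trial design {8}) and a failure rate of 1 − 0.92 = 0.08 (Sample size {14}).

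- Expected failures: 0.08 × 226 = 18.1.
- Approximate 95% range: 18.08 ± 1.96 × √(226 × 0.08 × 0.92) = 18.08 ± 7.99, or 10 to 26.
- With all 250 enrolled: 0.08 × 250 = 20.
- Events per variable, 18.1/k: 9.0 for two terms, 6.0 for three, 3.6 for five.
- At an assumed 10 events per variable, 18.1/10 = 1.8, so one term fits with a second marginal. At an assumed 5, 18.1/5 = 3.6, so three to four.

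**6. Noise admitted by screening at p < 0.1.** The article gives no candidate count. For m independent null candidates, the expected number admitted is 0.1m and the chance of at least one is 1 − 0.9^m.

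| m (assumed) | Expected admitted | Chance of at least one |
|---|---|---|
| 5 | 0.5 | 41% |
| 10 | 1.0 | 65% |
| 20 | 2.0 | 88% |

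Correlated candidates would change the right-hand column but not the expected number.

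**The case against.** The strongest case on the other side is that this is a loosely worded secondary prognostic analysis.

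- The Cox sentence names no outcome. It follows the time-to-event definition and the Kaplan–Meier sentence, so it may be meant for the 2-year composites. The link to the discharge endpoint comes only from the next sentence. This stands as a caution: the article does not establish that Cox regression will be run on discharge status. It does fix a selection rule against the primary endpoint.
- A reader might infer that randomised arm is left out of the model. The article does not support that. Arm is not named, but the entry rule speaks of factors in general and nothing excludes it.
- A reader might infer that the plan yields no treatment comparison. That is wrong for the plan as a whole, because chi-square, Kaplan–Meier and log-rank comparisons between arms are planned. Kaplan–Meier curves by arm also give 2-year event proportions. What is not stated is an effect estimate with an interval. An article may leave that to the analysis plan, but this article does state a regression, and directs it at something else.
- A reader might infer that the models will be overfitted. This is a conditional risk. The 18 failures apply only to the discharge endpoint, no event rate is given for the 2-year composites, and the numbers of candidate and retained terms are unknown.
- A reader might infer that few failures make confidence intervals too narrow. Sparse events usually widen them. Any undue narrowness would come from ignoring the selection step, and it has not been quantified here.
- The Cox analysis is never called confirmatory, and no objective is said to rest on it. This stands, and it limits the consequence.
- Whether left ventricular variables are collected cannot be settled, because the table of study investigations is not shown. The narrower statement, that no objective or endpoint uses them, is unaffected.

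**Conclusion.** The point holds as a mismatch in what the article states, not as missing detail. The Cox model is aimed at variables that serve no stated objective, its entry rule is tied to a binary discharge status, and it is not directed at the randomised comparison. Objective (c) is therefore left without a stated between-arm estimate and interval, which a test for difference cannot replace.

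The size of the screening problem is conditional. It is about 18 events and 6 per variable with three terms, if the rule is applied to the discharge endpoint at the planned 92% success. The 65% and 88% chances of admitting noise assume 10 or 20 independent null candidates. The primary sample size is not affected.

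**What to change.** In Statistical methods {20a}:

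- For the 2-year composites, state a Cox model with randomised arm as the term of interest and report the hazard ratio with its 95% confidence interval. Limit any adjustment to a few covariates named in advance. Say how components read only at a visit, such as NYHA class and valve dysfunction, are dated.
- Analyse the discharge endpoint as a binary outcome, as a risk difference with its confidence interval.
- Remove the p < 0.1 entry rule against the primary endpoint.
- Keep any left ventricular predictor analysis only as labelled exploratory work, with its outcome and candidate variables named.

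The cost is wording and the loss of one prognostic screening analysis. No extra patients, visits or measurements are needed. The hazard ratio interval does not by itself settle non-inferiority at 2 years. It has to be read against a margin, and the only margin the article states belongs to the primary endpoint.

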## Discussion

This research is highly significant, as a broader usage of CMR in the planning of TAVR might have an immense impact on the incidence of postinterventional kidney injury and might furthermore improve clinical outcome. What is more, TAVR-CMR also allows to plan TAVR via alternate routes, such as the subclavian or axillary artery, if a femoral approach is not possible. Thus, TAVR-CMR could represent a reasonable alternative to the current routine standard of TAVR-CT. With increasing age, aortic stenosis is a major burden for affected patients and, thus, represents a huge challenge for Western health care systems. With growing postoperative risk, patients are more likely to benefit from TAVR; however, especially these patients are at higher risk of suffering periinterventional kidney failure due to a high cumulative dose of contrast agent [13]. This patient population seems to be the main target group to profit from the alternative use of TAVR-CMR. What is more, CMR appeared to show higher accuracy than CT and 3D-echocardiography in assessing aortic annulus dimensions ex vivo as well as in vivo, while CT seemingly tends to underestimate annular size [25]. Due to the potential prevention of postinterventional kidney injury, CMR can also be expected to reduce costs albeit being more expensive upfront. Furthermore, chronic kidney disease and consequential renal replacement therapy have a massive impact on quality of life in terms of physical, functional, metabolic, social, and mental conditions [38], which again adds to treatment costs.

Anyway, we do acknowledge that our study bears some limitations. Firstly, TAVR-CMR is still not widely available and for now can be performed primarily in tertiary-care centers. Additionally, CT surpasses MRI especially in the characterization of aortic and valvular calcification, which indeed is a common concomitant feature of AV stenosis. Nevertheless, it can be assumed that neither vascular nor valvular calcifications will have a major impact on the planning of TAVR via CMR; according to Tsang et al., CMR and CT have a very good agreement in sizing the annular ring diameters independently of calcification grade [25]. Lastly, in patients with claustrophobia or other contraindications for MRI, TAVR-CMR can hardly be performed.

## Trial status

The trial protocol has been approved by Ethics Committee of Medical University Innsbruck. The study initiation was held in July 2019. Current study protocol version number 4.0 is basis for this manuscript and written in accordance with the Standard Protocol Items: Recommendations for Interventional Trials (SPIRIT) Statement.

## Data Availability

The datasets used and/or analyzed during the current study are available from the corresponding author on reasonable request.

## Abbreviations

3D: Three dimensional
ACC: American College of Cardiology
AE: Adverse event
AHA: American Heart Association
AV: Aortic valve
AVA: Aortic valve area
AVR: Aortic valve replacement
CMR: Cardiovascular magnetic resonance
CRF: Case Report Form
CT: Computed tomography
EC: Ethics Committee
ESC: European Society of Cardiology
MRA: Magnetic resonance angiography
MRI: Magnetic resonance imaging
SAE: Serious adverse event
TAVR: Transcatheter aortic valve replacement
TEE: Transesophageal echocardiography
TTE: Transthoracic echocardiography
VARC: Valve Academic Research Consortium
